### **3.3.2 Secondary Outcomes**

- 
1. Changes in CKD diagnosis rate: the difference in the proportion of CKD patients with an ICD-code for CKD documentation between the follow-up and baseline periods.
  2. Changes in utilization of renoprotective medications: the difference in prescription rates of RAASi and SGLT2i among CKD patients between the follow-up and baseline periods, reported separately.
  3. Changes in screening rate for CKD: the difference in the proportion of patients at high risk for CKD who complete SCr and/or urine protein testing between the follow-up and baseline periods.
  4. Changes in renal referral rate: the difference in the proportion of CKD patients meeting criteria for nephrologist consultation referral who are actually referred.
  5. Changes in blood pressure control rate: the difference in proportion of CKD patients achieving a target of <130/80 mmHg, based on available tests.
  6. Changes in glycemic control rate: the difference in the proportion of CKD patients achieving a HbA1c <7%, based on available tests.
  7. Changes in lipid control rate: the difference in the proportion of CKD patients achieving a LDL-C <2.6 mmol/L, based on available tests.
  8. Cost-effectiveness of the CKD-CDSS: economic evaluation of the community-based CKD screening and management program.
  9. CDSS implementation process: process evaluation using the RE-AIM framework (**Table 5**) to understand the implementation of this complex intervention. This evaluation examines the factors influencing outcomes across five dimensions—Reach, Effectiveness, Adoption, Implementation, and Maintenance—at both the individual and organizational levels. An initial phase, structured questionnaires for community institutions and physicians (**Table 6**) will be used to inform the timely optimization of the CDSS and its implementation strategy.

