### 3. Research Design

This study employs a multicenter, parallel-group, cluster-randomized controlled trial design. A total of 30 community health centers in the Xicheng District of Beijing will be recruited, with each center constituting a cluster. The study population consist of adult CKD patients and patients at high-risk for CKD-who are regularly managed at these centers, defined as having two or more visits documented in the Electronic Health Record (EHR) system during a designated 12-month screening period. Baseline characteristics, including CKD diagnosis (based on ICD codes) and clinical measures (e.g., the most recent blood pressure, HbA1c, and LDL-c values), were all ascertained from data recorded during this screening period. These 30 clusters will be stratified by their annual patient visit volume (large, medium, small) and subsequently randomized in a 1:1 ratio to either the intervention or control group. Following randomization and prior to the formal initiation of the intervention, both groups will receive the government-supported structured training. The intervention group will then implement a CKD-specific CDSS integrated into their existing EHR platforms, in addition to providing government-supported structured training. The control group will continue with usual care, also supplemented by the same government-supported training to isolate the effect of the CDSS itself. The trial will employ a two-phase evaluation scheme: a 6-month initial phase assessing the impact of the CDSS on process measures (CKD diagnosis, RAASi/SGLT-2i use) and short-term clinical control rates (blood pressure, HbA1c, LDL-c), and the final 36-month phase evaluating its effects on the primary composite endpoint of kidney and cardiovascular hospitalization rates, alongside a comprehensive health economic analysis, which will be conducted through linkage with the centralized Beijing Health Insurance Database.

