### 3.2.1 CDSS

The CDSS will be developed using a Plan-Do-Check-Act framework and will be integrated into the existing EHR system. In the Plan phase, semi-structured interviews with PCPs will be conducted to identify user needs. The Do phase will involve a multidisciplinary team (including nephrologists, technical experts, and PCP representatives) in designing an initial prototype. A pilot study at an independent primary care center will then be conducted as the Check phase, during which the system will be iteratively refined. Finally, the Act phase will consist of evaluating the system's effectiveness and implementation feasibility through the main clinical trial described above. The CDSS is designed to provide non-intrusive, real-time clinical decision support during patient encounters. The key functionalities deployed in the intervention arm include:

1. Automated case identification & risk stratification: The system automatically identifies patients with or at risk of CKD through structured diagnostic codes and laboratory data.

2. Renal referral for patients without prior diagnosis of CKD

- (1) Rapid decline in renal function meeting the AKD criteria (**Table 3**).

- (2) Presence of refractory hypertension: defined as blood pressure (BP) >140/90 mmHg while prescribed  $\geq 3$  antihypertensive medications, or being prescribed  $\geq 4$  classes of antihypertensive medications.

- (3) Persistently proteinuria, hematuria or eGFR <60 mL/min/1.73m^2 (two consecutive abnormal results obtained  $\geq 90$  days apart)

3. Automated CKD staging (stages 1-5)

4. Structured management protocols for diagnosed CKD patients:

- (1) Stage-specific monitoring of renal function (e.g., eGFR, UACR every 3 month).

- (2) Complication management alerts for identification, evaluation and management targets based on thresholds defined as follows: hypertension (BP >130/80 with proteinuria or >140/90 without), CKD-mineral and bone disorder (CKD-MBD) (corrected Ca2+ <2.2 mmol/L; PO4 >1.61 mmol/L), hyperkalemia (K+ >5.5 mmol/L), metabolic acidosis (pH <7.25 or HCO3 <22 mmol/L), anemia (Hb <120 g/L [Male] / <110 g/L [Female]), and dyslipidemia (LDL-C >1.8 mmol/L).

5. Renal referral for CKD patients presenting with following indications:

- (1) Advanced CKD (stage 4-5)

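### BP, HbA1c and LDL-C control rates are restricted to patients with follow-up tests, a post-randomisation subset that the CDSS may alter; the referral denominator is exposed more directly

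*Protocol*

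**What the plan says.** Protocol section 3.3.2 restricts three secondary outcomes to patients who have a measurement:

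- Item 5, blood pressure: "the difference in proportion of CKD patients achieving a target of <130/80 mmHg, based on available tests".
- Item 6, glycaemia: "the difference in the proportion of CKD patients achieving a HbA1c <7%, based on available tests".
- Item 7, lipids: "the difference in the proportion of CKD patients achieving a LDL-C <2.6 mmol/L, based on available tests".

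Item 4, referral, lacks that restriction, but its denominator also depends on test results: "the difference in the proportion of CKD patients meeting criteria for nephrologist consultation referral who are actually referred".

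Baseline status comes from records of the screening year. Section 3 names "clinical measures (e.g., the most recent blood pressure, HbA1c, and LDL-c values" among the sources.

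In the intervention arm only, section 3.2.1 item 4 adds scheduled renal monitoring, "Stage-specific monitoring of renal function (e.g., eGFR, UACR every 3 month", and a set of alerts: "Complication management alerts for identification, evaluation and management targets based on thresholds defined as follows". The alert list includes hypertension and dyslipidaemia but not glycaemia. Section 4 adds weekly feedback on quality indicators tied to the CDSS.

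Section 3.6.2.1 commits every analysis to intention to treat. It imputes variables with less than 20% missing and drops variables with more than 20% missing. It does not say whether outcomes are included.

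**The concern.** The cohort is fixed from visits in the screening year (section 3.1.1), so a denominator that allocation cannot affect already exists. The restriction to available tests replaces it with a subset formed after randomisation. If the CDSS changes which patients are measured, the two tested subsets can differ even when true control is identical, and randomisation no longer protects the comparison.

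Item 4 has a parallel problem. CKD patients qualify for referral through findings such as stage 4-5 disease, rapid eGFR decline or UACR of at least 300 mg/g (section 3.2.1 item 5). These are known only if tested, and eGFR and UACR are the two tests named in the CDSS monitoring schedule. The intervention can therefore enlarge its own denominator with newly detected patients, whose chance of referral may differ from that of patients found under usual care.

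The control rates are the short-term clinical results of the 6-month phase, so they will be read well before the 36-month primary endpoint.

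**Working it through.** **No stated figure to reproduce.** The protocol gives no testing rate, expected effect or power for these outcomes. All testing and control rates below are assumptions. They show how the rule behaves and do not predict this trial.

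**Step 1. Observed rate under the available-tests rule.** Let p be the true control rate, and t_c and t_u the probabilities of being tested for controlled and uncontrolled patients. Then

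observed rate = p·t_c / (p·t_c + (1 − p)·t_u).

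Dividing through by t_u shows that only the ratio t_c/t_u matters. With the same p in both arms, the spurious difference is zero when the ratio is the same in both arms. A higher testing rate alone does not bias the comparison; a change in who is tested does.

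**Step 2. No true effect, p = 0.40 in both arms.**

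| Pattern | Control arm t_c / t_u | CDSS arm t_c / t_u | Observed control arm | Observed CDSS arm | Spurious difference |
|---|---|---|---|---|---|
| a | 0.40 / 0.60 | 0.70 / 0.70 | 0.16/0.52 = 30.8% | 0.28/0.70 = 40.0% | +9.2 points |
| b | 0.50 / 0.50 | 0.50 / 0.70 | 0.20/0.50 = 40.0% | 0.20/0.62 = 32.3% | −7.7 points |
| c | 0.70 / 0.80 | 0.85 / 0.85 | 0.28/0.76 = 36.8% | 0.34/0.85 = 40.0% | +3.2 points |

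Over p = 0.30 to 0.50 and six testing patterns, the difference ran from −8.3 points (p = 0.50, pattern b: 0.25/0.60 = 41.7% against 50.0%) to +13.8 points (p = 0.50, control arm 0.40/0.60, CDSS arm 0.70/0.60: 0.35/0.65 = 53.8% against 0.20/0.50 = 40.0%).

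**Step 3. What missing tests leave undetermined.** For an observed rate of 40% and an untested share q, the full-cohort rate lies between 0.40(1 − q) and 0.40(1 − q) + q. At q = 20% that is 32% to 52%; at q = 50% it is 20% to 70%.

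**Step 4. Does counting untested patients as not at target repair it?** Suppose half of each arm is routinely monitored with 50% controlled, and half is not monitored with 30% controlled. True control is 0.5×0.5 + 0.5×0.3 = 40% in both arms. The control arm tests only the first half; the CDSS arm also tests half of the second.

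- Available tests: control 50.0%; CDSS (0.5×0.5 + 0.25×0.3)/0.75 = 43.3%. Spurious difference −6.7 points.
- Untested counted as not at target: control 0.5×0.5 = 25.0%; CDSS 0.25 + 0.25×0.3 = 32.5%. Spurious difference +7.5 points.

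The second rule does not remove the error. Extra testing can only add successes, so it favours the arm that tests more.

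**Step 5. The missing-data rule set beside the outcome definition.** If 3.6.2.1 covers outcomes, untested patients are imputed below 20% missing, which contradicts the restriction in 3.3.2; above 20% the outcome is dropped. In pattern a the untested shares are 48% and 30%, and in pattern b 50% and 38%, so the outcome would disappear in either case. If 3.6.2.1 covers only covariates, the tested-only rule stands. The protocol does not say which reading applies.

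**The case against.** The strongest reply is that differential testing is not documented for these three measures. The scheduled monitoring names eGFR and UACR as examples, and neither feeds the BP, HbA1c or LDL-C rates. The hypertension and dyslipidaemia alerts use thresholds on values, so they seem to need a recorded value before they fire. Glycaemia appears only in treatment recommendations. Both arms are trained on monitoring intervals (section 3.2.2), and cohort members had at least two visits in the screening year, so BP in particular may be recorded for most of them (an assumption).

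Much of this stands. A reader might infer that the CDSS decides who is tested for BP, HbA1c and LDL-C, and hence that the arms will be differently selected. The protocol does not support that as fact. For BP and LDL-C an effect on testing is inferred from the identification and evaluation role of the alerts and from the weekly feedback; for HbA1c the link is weakest.

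The reply does not remove the point. Training given to both arms leaves the CDSS contrast in place, and the outcome definition conditions on a post-randomisation event whatever the size of the effect. Nor does it answer the referral problem, where the scheduled tests are the ones that determine eligibility.

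A second objection is that 3.6.2.1 may already deal with missing outcomes. It may, but only by contradicting 3.3.2 or by dropping the outcome. A statistical analysis plan, not available for this review, might settle which reading applies; the protocol text would still need to agree with it.

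**Conclusion.** The point holds as a risk built into the outcome definitions. Items 5 to 7 condition on having a follow-up measurement, which fits poorly with intention to treat for all analyses, and item 4 has a denominator that the intervention can change directly. That follows from the text.

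Whether bias will occur, how large it will be and in which direction cannot be derived from the protocol. The range of −8.3 to +13.8 points rests wholly on assumed testing patterns. Two stronger conclusions should be resisted: that the control rates will favour the CDSS (the sign goes either way), and that counting untested patients as failures is a safe main analysis (Step 4 shows a false 7.5-point benefit).

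The change should be made, because these are the early clinical results and it is cheap. It does not touch the hospitalisation endpoints, which do not depend on community BP, HbA1c or LDL-C tests.

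**What to change.** 1. Reconcile 3.3.2 with 3.6.2.1, and state that the 20% exclusion rule does not apply to outcomes.
2. Define the analysis population for items 5 to 7 as all baseline-eligible patients in the randomised centres. For HbA1c, settle whether this means diabetic kidney disease (section 2.2.2, objective 6) or all CKD patients (section 3.3.2, item 6).
3. Handle untested patients by multiple imputation or inverse-probability weighting, using baseline values and covariates and respecting the clustering by centre.
4. Report the proportion tested by arm for each measure. Step 1 shows that this alone cannot confirm or exclude bias, so it accompanies the analyses in points 3 and 5.
5. Keep the available-tests rate as a sensitivity analysis and add bounding analyses. Counting untested patients as not at target may be one of these, but not the main analysis.
6. For referral, add an analysis in patients who met the criteria on screening-year data, beside the one that includes patients who newly qualify.

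The cost is wording and some extra analysis; no new data are needed. Imputation and weighting rest on a missing-at-random assumption. They are weakest for patients with no baseline value, and weighting cannot recover a group in which nobody is tested, such as the unmonitored half of the control arm in Step 4; there the bounds carry the message. The screening-year referral denominator leaves out newly eligible patients, so both referral analyses should be shown.

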#### **2.2.2 Secondary Objectives**

##### **Process Measures:**

1. To assess the effect of the CDSS on the underdiagnosis of CKD, as measured by the rate of appropriate ICD-coded documentation in patient records.
2. To examine the change in the utilization rates of renoprotective medications (RAASi and sodium-dependent glucose transporters 2 inhibitor [SGLT2i]) among CKD patients.
3. To evaluate the impact of the CDSS on the screening rate for CKD (SCr and/or urine protein testing) among patients at high risk for CKD.
4. To determine the effect of the CDSS on the referral rate of CKD patients who meet guideline-based criteria for nephrology consultation.

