##### **Clinical Outcome Measures:**

5. To evaluate the effect of the CDSS on blood pressure control (target: <130/80 mmHg) among patients with CKD.
6. To assess the impact of the CDSS on glycemic control (target: HbA1c <7%) among patients with diabetic kidney disease.
7. To examine the effect of the CDSS on lipid management (target: LDL-C <2.6 mmol/L) among patients with CKD.

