- (2) With any of the following complications: rapid eGFR decline meeting AKD criteria; persistent hematuria ( $\geq 20$  RBCs/HPF,  $\geq 80$  RBCs/ $\mu$ L, or occult blood  $\geq 2+$ ) on consecutive tests; refractory hypertension; hypoproteinemia (serum albumin <35g/L); CKD-MBD; severe anemia (Hb <100 g/L); significant proteinuria (UACR  $\geq 300$  mg/g

---

or UTP  $\geq 1.0$  g/day, or  $\geq 0.5$  g/day in diabetics); or persistent hyperkalemia ( $K^+ > 5.5$  mmol/L after initial treatment).

6. Treatment recommendations for CKD patients:

(1) SGLT2is are recommend as first-line treatment for patients with T2DM and an eGFR  $\geq 30$  mL/min/1.73 m^2.

(2) GLP-1 RAs are introduced for patients with T2DM and suboptimal glycemic control on metformin and SGLT2i, with eGFR  $\geq 15$  mL/min/1.73 m^2.

(3) RAASi are recommended for patients with proteinuria and/or hypertension, contingent upon the following criteria: eGFR  $\geq 30$  mL/min/1.73 m^2 (within the past 6 months), serum  $K^+ < 5.5$  mmol/L (within the past 6 months), and absence of bilateral renal artery stenosis.

(4) Dosing for all relevant medications should be adjusted according to renal function, as specified in **Table 4**.

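### Secondary outcome 6 counts HbA1c control in all tested CKD patients, whereas its objective is confined to diabetic kidney disease

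*Protocol*

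**What the plan says.** Protocol Section 2.2.2 (Clinical Outcome Measures, item 6) sets the objective as "glycemic control (target: HbA1c <7%) among patients with diabetic kidney disease". Section 3.3.2, item 6, defines the matching outcome as "the difference in the proportion of CKD patients achieving a HbA1c <7%, based on available tests". Section 3.1.2.1 admits patients to the CKD cohort on repeated low eGFR, on confirmed proteinuria, or on a CKD code with one qualifying result; diabetes is not among the conditions. Section 3 lists HbA1c control among the short-term results of the six-month phase, so this outcome is reported early.

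Two neighbouring outcomes bear on how far the point reaches. Outcome 2 is "the difference in prescription rates of RAASi and SGLT2i among CKD patients between the follow-up and baseline periods, reported separately", and its objective in Section 2.2.2 (Process Measures, item 2) names the same CKD population. Outcome 5 scores blood pressure against 130/80 mmHg in CKD patients, as objective 5 does. Section 3.2.1 gives narrower rules for the CDSS itself: "SGLT2is are recommend as first-line treatment for patients with T2DM and an eGFR" of at least 30; "RAASi are recommended for patients with proteinuria and/or hypertension, contingent upon the following criteria" on eGFR, potassium and renal artery stenosis; and a complication alert for "hypertension (BP >130/80 with proteinuria or >140/90 without".

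**The concern.** One endpoint is given two populations. A statistical analysis plan can add detail, but it cannot follow both sentences.

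If the outcome wording is followed, patients without diabetes who happen to have an HbA1c enter both numerator and denominator. Almost all of them are below 7% whatever their physician does. This has two consequences. First, the contrast between arms shrinks in proportion to the diabetic share of those tested. Second, because the denominator is whoever was tested, a change in the mix of tested patients that differs between arms would move the control rate without any change in glycaemic control.

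**Working it through.** **Figure to reproduce.** There is none. Section 3.6.1 gives sample size and power for the primary outcome only.

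**Inputs from the protocol (Section 3.6.1).** 30 centres, 15 per arm; total 3,240, hence 1,620 per arm and 3,240 / 30 = 108 per centre; ICC 0.02; significance level 0.05 (taken as two-sided).

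**Assumed inputs, not in the protocol.** Control rate in diabetics 60% (control arm) and 70% (intervention arm); 98% in non-diabetics in both arms; all 1,620 per arm have an HbA1c; diabetic share f among those tested of 0.8, 0.6 or 0.4.

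**Dilution.** The control rate among all tested is f × (rate in diabetics) + (1 − f) × 0.98. The non-diabetic term cancels between arms, so the observed difference is f × 10 points.

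**Power.** Normal approximation for two proportions on the effective sample size per arm.
- All tested: 1,620 / (1 + 107 × 0.02) = 1,620 / 3.14 = 516.
- Diabetics only: 1,620f / (1 + (108f − 1) × 0.02). This gives 1,296 / 2.708 = 479, 972 / 2.276 = 427 and 648 / 1.844 = 351 for the three shares.

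| f | All tested, control → intervention | Difference | Power, all tested | Power, diabetics only (60% → 70%) |
|---|---|---|---|---|
| 0.8 | 67.6% → 75.6% | 8 points | 81% | 90% |
| 0.6 | 75.2% → 81.2% | 6 points | 65% | 87% |
| 0.4 | 82.8% → 86.8% | 4 points | 43% | 79% |

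In each row the restricted analysis has fewer patients and more power. The comparison is unadjusted and uses follow-up proportions only. It shows relative loss and does not forecast the trial's power.

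**Change of mix.** With no treatment effect, a gap of 10 points between arms in the non-diabetic share of those tested shifts the control rate by 0.10 × (0.98 − 0.60) = 0.038, or 3.8 points. Because outcome 6 is a change from baseline, the gap must arise after baseline; one present in both periods would cancel.

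**The case against.** - **Tested patients may be mostly diabetic.** The outcome covers only patients with an available HbA1c. This is a fair point: at a share of 80% the loss is 2 points of effect and about 9 points of power. The protocol gives no share, so higher values belong in the range.
- **The adjusted model contains diabetes.** Section 3.6.2.1 adjusts secondary outcomes for comorbidities including diabetes. That should remove much of the change-of-mix problem from the adjusted estimate. It does not change the population, and the unadjusted estimate and the control rates themselves stay exposed.
- **No arm difference in testing is shown.** The CDSS monitoring rule in Section 3.2.1 gives eGFR and UACR as its examples and does not mention HbA1c. The 3.8 points are therefore a possibility and not an expected bias.

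Stronger readings are tempting, but the protocol does not support them.

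- A reader might infer that outcomes 2 and 5 are wrong in the same way because they include patients whom the CDSS does not address. Their objectives name the same CKD population, and an all-CKD rate is a legitimate estimand for a trial that calls itself pragmatic. For blood pressure, a patient without proteinuria between the two thresholds does not trigger the complication alert, but the RAASi recommendation for hypertension carries no blood pressure cut-off and may still reach that patient.
- A reader might also square the reciprocal of the share and conclude that at 40% diabetic (1 / 0.4)² = 6.25 times as many patients are needed. That supposes equal variance, which conflicts with the premise that non-diabetics are nearly all below 7%. With the inputs above, the variances at the average rates are 0.129 (all tested) and 0.2275 (diabetics), so the ratio is 6.25 × 0.129 / 0.2275, or about 3.5. Within one fixed cohort, where restriction discards 60% of patients, it is 3.5 × 0.4, or about 1.4 ignoring clustering.

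**Conclusion.** The point holds for HbA1c. Objective 6 and outcome 6 name different populations, and the outcome as written does not measure the objective. That conclusion rests on the text alone and needs no assumption.

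The direction of the dilution follows if patients without diabetes have no effect on this endpoint. Its size cannot be fixed from the protocol: under the assumed inputs it runs from mild (8 of 10 points kept at a share of 80%) to serious (4 of 10 points, and power of 43% against 79%, at 40%). The outcome is secondary, so the primary sample size is unaffected, but the wording should be corrected before the six-month results are reported.

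For outcome 2 there is no error, only room for a supporting analysis. For outcome 5, the endpoint target and the complication-alert threshold without proteinuria differ, and the two passages must be reconciled; nothing is said here on which is right.

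**What to change.** **Needed.** In Section 3.3.2, item 6, replace the CKD population by CKD patients with T2DM recorded in the screening year, and state that this is the operational definition of diabetic kidney disease in objective 6. Without that statement one mismatch replaces another. The diagnosis codes are already used for eligibility, so the cost is a change of wording and a smaller denominator. The restriction does not remove selective testing among diabetics; reporting the number tested per arm and period would show it.

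**Optional for outcome 2.** Keep the all-CKD rates and add SGLT2i and RAASi rates among patients eligible under the CDSS rules on screening-year data. For SGLT2i, Section 3.2.1 item 6(1) (eGFR of at least 30) and Table 4 (contraindication reminders below 60 or 45, depending on the drug) conflict and must be reconciled first. For RAASi, a rule is needed for patients without a recent eGFR or potassium value.

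**Outcome 5.** Reconcile the endpoint target with the alert threshold in Section 3.2.1 item 4(2), or report blood pressure control by baseline proteinuria.

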## **3.6 Statistical Analysis**

### **3.6.1 Sample Size and Statistical Power**

The primary outcome is a composite hospitalization rate for kidney-related (acute kidney injury, progression of kidney disease, or requiring dialysis) or cardiovascular events (myocardial infarction, stroke, heart failure, or cardiovascular procedures). Based on data from the US CRIC cohort, the all-cause hospitalization rate for CKD patients is 35.0 per 100 person-years. The sample size calculation aims to detect a 20% reduction in this rate following 36 months of CDSS intervention, compared to usual care. The calculation is performed using cluster randomization tools (online calculator at <https://clustercts.shinyapps.io/rshinyapp/>) with the following parameters: 30 randomized centers (15 per arm), an intraclass correlation coefficient of 0.02, and a significance level of 0.05. A total sample size of 3,240 participants is estimated to provide 90% statistical power (**Figure 1**).

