### **3.6.2 Data Analysis**

#### **3.6.2.1 Analysis Principles**

Categorical variables will be described as frequencies and percentages. Continuous variables will be summarized as means with standard deviations or as medians with interquartile ranges, based on their distribution. The primary outcome of hospitalization rate will be analyzed using generalized linear mixed models (GLMMs). Both unadjusted and adjusted estimates will be presented; adjusted analyses will include age, sex, comorbidities (including diabetes, hypertension, and cardiovascular disease), and baseline eGFR. Other secondary outcomes will be analyzed using the same approach but without adjustment for baseline eGFR.

For missing data, if the proportion of missingness is below 20%, continuous variables will be imputed using regression-based methods and categorical variables using predictive mean matching. Any variable with over 20% missing values will be excluded from the analysis.

All analyses will adhere to the intention-to-treat (ITT) principle. Given the pragmatic trial setting, a decline in adherence is anticipated. Should adherence to the CDSS intervention fall below 60%, a secondary as-treated (AT) analysis will be performed as pre-specified. All statistical analyses will be conducted using RStudio (v2022.02.03).

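### The adjusted model for the three control-rate outcomes (items 5–7) leaves out each measure's own baseline value, which the trial already extracts; adding it is a cheap likely gain in precision

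*Protocol*

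**What the plan says.** Lipid control appears as an outcome only in the form of a rate. The secondary objective in 2.2.2 reads "lipid management (target: LDL-C <2.6 mmol/L", item 7 of 3.3.2 is "the difference in the proportion of CKD patients achieving a LDL-C <2.6 mmol/L", and section 3 lists it for the six-month phase among "short-term clinical control rates (blood pressure, HbA1c, LDL-c". Items 5 and 6 treat blood pressure and HbA1c likewise, as proportions at target among patients with available tests.

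Section 3.6.2.1 plans generalized linear mixed models with unadjusted and adjusted estimates. For the primary outcome, "adjusted analyses will include age, sex, comorbidities (including diabetes, hypertension, and cardiovascular disease), and baseline eGFR". Secondary outcomes follow the same approach with baseline eGFR removed, which leaves age, sex and comorbidities. The same section imputes variables with less than 20% missing and drops those with more.

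Section 3 states that baseline data from the screening period include "clinical measures (e.g., the most recent blood pressure, HbA1c, and LDL-c values".

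**The concern.** The baseline value of an outcome is usually among its strongest predictors. The protocol does not leave the covariates open. It names a list and makes a specific exception for secondary outcomes, and under that rule no control-rate outcome is adjusted for its own starting value. The values exist in the baseline extract, so the omission saves nothing.

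At stake is the width of the confidence intervals for three secondary clinical outcomes in the six-month readout. The choice of covariates does not bias the randomized comparison, and neither hospitalization endpoint is touched.

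**Working it through.** **No planned figure to reproduce.** The protocol gives no sample size or power for items 5–7. The calculation below is for LDL-C; none was made for blood pressure or HbA1c.

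**Inputs from Protocol 3.6.1.** 30 centers and 3,240 patients, so 3,240/30 = 108 per center; and "an intraclass correlation coefficient of 0.02". That coefficient was set for hospitalization and is borrowed here for LDL-C.

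**Assumptions not in the protocol.** Equal center sizes; normally distributed LDL-C with mean 2.4–2.8 and SD 0.8–0.9 mmol/L; an intervention effect of 0.2 mmol/L; patient-level baseline to follow-up correlation r of 0.5 or 0.7; center-level correlation rc equal to r, 0.3 or 0.

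**Step 1: baseline covariate, continuous LDL-C.** Variance of a center mean, adjusted over unadjusted, with m patients per center:

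ratio = [0.02(1 − 2·r·rc + r²) + 0.98(1 − r²)/m] / [0.02 + 0.98/m]

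With m = 108 the denominator is 0.02 + 0.00907 = 0.02907.

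| r | rc | numerator | ratio |
|---|---|---|---|
| 0.5 | 0.5 | 0.02(0.75) + 0.00681 = 0.02181 | 0.750 |
| 0.7 | 0.7 | 0.02(0.51) + 0.00463 = 0.01483 | 0.510 |
| 0.5 | 0.3 | 0.02(0.95) + 0.00681 = 0.02581 | 0.888 |
| 0.7 | 0.3 | 0.02(1.07) + 0.00463 = 0.02603 | 0.895 |
| 0.5 | 0 | 0.02(1.25) + 0.00681 = 0.03181 | 1.094 |
| 0.7 | 0 | 0.02(1.49) + 0.00463 = 0.03443 | 1.184 |

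So variance falls by 25–49% when rc = r and by 10–11% at rc = 0.3, and rises by 9–18% at rc = 0. With 50 tested patients per center, the same formula gives a cut of 15–21% at rc = 0.3 and is neutral at rc = 0 (1.003–1.005).

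**Step 2: baseline covariate, <2.6 rate.** By simulation on the rate scale, m = 108, the ratio is 0.77–0.80 at r = rc = 0.5, 0.59–0.60 at r = rc = 0.7 and 0.90–0.93 at rc = 0.3. These are cuts of 20–41%, or 7–10% at rc = 0.3.

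**Step 3: does the change wording already do this?** Item 7 is headed as a change in the control rate, so baseline status could enter by subtraction. The variance of that change, relative to the follow-up rate alone, is 0.78–1.17 with rc = r and 1.21–1.38 at rc = 0.3. Differencing recovers little and can lose precision.

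**Step 4: cost of the cut-off itself.** For a uniform 0.2 mmol/L fall, unadjusted, the <2.6 rate keeps 83–85% of the information in continuous LDL-C at m = 108 (76–78% at m = 50, 92–93% at m = 300). Most of the available gain therefore comes from the baseline value, not from the scale.

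**Step 5: in terms of power.** A separate simulation used 30 × 108 patients, SD 0.8, a 0.12 mmol/L shift, 50% at target and rc = 0.7. Power was 0.56–0.57 for the follow-up proportion and 0.77, 0.84 and 0.91 for baseline-adjusted continuous LDL-C at r = 0.3, 0.5 and 0.7. At rc = 0.3 and r = 0.5 the rise was from 0.56 to 0.68.

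**The case against.** - **Nothing stated is wrong.** The proportion at a clinical target is a legitimate outcome, and a supportive analysis or an extra covariate is often left to a statistical analysis plan. The first half stands, which is why this is an optional improvement. The second half does not fully answer the point, because the protocol itself fixes the covariate rule for secondary outcomes.

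- **The comparator is generous.** The cuts above are against no covariates, whereas the protocol already adjusts for age, sex and comorbidities. This stands; the gain over the planned model is unknown.

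- **Size and even sign depend on assumptions.** This stands. The continuous result runs from a 49% cut to an 18% increase. The increase requires that a center's baseline and follow-up LDL-C levels be uncorrelated, and it vanishes at about 50 tested patients per center.

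- **On the odds-ratio scale the variance does not fall.** Section 3.6.2.1 names no link function. With a logit link, 30 × 108 patients, mean 2.6, SD 0.85, a 0.2 fall and r = rc = 0.5–0.7, adjustment moved the odds ratio from about 1.45 to 1.56–1.74 and raised the variance of its logarithm by 13–28%, although test information improved. This stands, so the fix must name the effect measure.

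- **The covariate may be unavailable.** Inclusion rests on visits, not on an LDL-C test, and the 20% rule could remove it. This stands, and the fix provides for it.

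A reader might infer a stronger fault from section 3.2.1. The system alerts for "dyslipidemia (LDL-C >1.8 mmol/L" while success is <2.6, so a fall within 1.8–2.6 does not register. For blood pressure, "hypertension (BP >130/80 with proteinuria or >140/90 without", an alerted patient is never inside the <130/80 target. The documents do not support calling this a defect. An alert threshold need not equal a success threshold, and falls from 2.6 or above do register. If only alerted patients fall, the <2.6 rate keeps 87–113% of the continuous information, no worse than the 83–85% under a uniform fall. The mismatch is not a material source of loss, nor a reason to single out lipids.

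**Conclusion.** The point holds as a low-priority improvement: the stated adjusted model for items 5–7 omits the baseline value of the outcome although it is already extracted. For LDL-C, relative to no covariates, the likely benefit is a variance reduction of 25–49% (continuous) or 20–41% (rate scale) if patient- and center-level correlations are both 0.5–0.7. It is about 10% if the center-level correlation is 0.3, with no gain or a loss near zero. All of this rests on an assumed LDL-C distribution and assumed correlations, on equal centers and on the borrowed coefficient of 0.02. The reasoning carries over to blood pressure and HbA1c, but their gain has not been computed. The lipid comparison should not be read as biased or invalid, and the primary endpoints are unaffected.

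**What to change.** Add to 3.6.2.1, after the sentence on secondary outcomes:

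*For outcomes 5–7 the adjusted model also includes the baseline value of the same measure. The between-arm effect is reported as a standardised difference in proportions, and the unadjusted estimate is still presented.*

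Keep the <2.6 definition in item 7 and add:

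*Supportive: the between-arm difference in follow-up LDL-C (mmol/L) as a continuous value among CKD patients with available tests, from a mixed model with center as random effect and baseline LDL-C as covariate. If baseline LDL-C is missing in over 20% of these patients, outcome 7 is reported without that covariate.*

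The cost is two insertions and one more secondary analysis, with no new data collection. Below 20% missing, the existing rule imputes the baseline value. If those patients were dropped instead (108 × 0.8 ≈ 86 per center), the continuous variance ratio would be 0.810 at r = rc = 0.5 and 0.551 at 0.7, a cut of 19–45%, or 5–6% at rc = 0.3. Above 20%, only the comparison without baseline LDL-C remains. Selection by available tests is unchanged.
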